**6.52 Selenium Supplements**

The supplements and the placebos will be produced and supplied by a company calledPharmaNord (Denmark) who will make the pressed tablet containing high selenium-yeast. The placebo tablet will be visually identical to the doses but will contain yeast containing no selenium. The supplements used in this study will be from the same batch as those to be used in a human study being carried out at the University of Liverpool, due to start next year. The supplements will be supplied blind to the Institute and labelled either A, B, C or D. The possibility of assessment bias will be avoided by using a double blind assessment. The volunteers will receive their supplements in a blister pack labelled either, A, B, C or D. The supplements will be taken everyday with breakfast from the day of the first blood sample (Day 0). The volunteers will be asked to keep track of when they take their supplement each day by ticking the appropriate box on the record sheet provided. We will request that the manufacturers of the tablets maintain a copy of the code for the supplements and that a copy of the code be sent to us to be held by [name] (HNU manager) in the case of a serious adverse event where we would need to know the dose being taken by the volunteer.

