# 4.0 Study Design

## 4.1 Overview

A 12 week intervention will be carried out in which 6 groups of 50-64y old men and women (n=24 per group) with low plasma (or serum) selenium are fed one of three doses of selenium (50, 100 or 200µg/d) as selenium enriched yeast (Se-yeast) tablet, a placebo tablet, selenium-enriched onions (equivalent to 50µg/day selenium) or un-enriched onions during the summer, autumn and winter periods (July-February). Subjects will be given an influenza viral challenge 10 weeks after starting the intervention. Volunteers will be informed that our study also vaccinates during the months December to February which is outside the traditional flu vaccination period adopted by the NHS. The precise time of vaccination for the volunteers will depend on their intervention starting date and may therefore take place in the period between December to February. Health care workers and those who are offered free flu vaccination from the NHS will not be eligible to take part in the study during the months of December to February.

The Se-yeast treatment will take place over 3 years; the onion treatment will take place during years 2 and 3 (the onions will be grown in years 1 and 2 for consumption the following year). The onions will be stored for a number of months and then incorporated into meals which will be stored at -18°C until required.

The control subjects will take a placebo and undergo the same tests. Venous blood samples will be taken pre-vaccination at baseline (week 0, 80mls), 6 (40mls) and 10 weeks (80mls) then post vaccination at 11 (80mls) and 12 weeks (80mls). Saliva samples will be obtained at baseline (pre-vaccination) and 12 weeks (post-vaccination). Blood samples will be used for the assessment of plasma selenium concentration (Q-ICPMS), plasma vitamin E (HPLC), selected selenoproteins, selenium-responsive genes, protein expression, and cellular and humoral immune response. The saliva samples will be tested for antibody titres to influenza antigens. A 24hour urine collection will be made during week 6 to determine selenium concentration.

Week 0

6

10

11

12

[figure not shown]

Up to 5 onion based test meals consumed

per week for 12 weeks

[figure not shown]

-Se

+Se

1 capsule taken every day for 12 weeks

Fasted Blood sample (60mL)

24hour urine collection

Influenza virus vaccination

Volunteer groups taking part in study

Saliva sample

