## Volunteers will be stratified by sex.

## 6.1 Supplementation Intervention with Se-yeast

Se-yeast supplementation (groups 1-4) will be studied during years 1, 2 and 3 of the project. All the pressed tablets will be identical (bar alphabetical labelling which will be carried out at manufacture) and will be labelled according to the law. Safety advice will also be given when the tablets are handed to the volunteers. One tablet will be taken each day for 12 weeks. The volunteers will also be given a record sheet where they will be asked to indicate at which times the supplement was taken each day (Annex 16).

Group 1: Se-yeast tablet (50μg Selenium/day)

Group 2: Se-yeast tablet (100μg Selenium /day)

Group 3: Se-yeast tablet (200μg Selenium /day)

Group 4: Placebo (control group).

On Day 1 of the study, the volunteer will be asked to attend the unit in the morning between the hours of 7:30 and 9:00am to give their first fasting blood and saliva sample. A scientist from the study team will be on hand to ensure that the volunteer is relaxed and comfortable. The volunteers will be asked not to brush or floss their teeth prior to arriving at the Unit as the use of toothpaste may interfere with the saliva sample to be collected. The volunteer will however be encouraged to bring their toothbrush and tooth paste with them to the unit so they may brush their teeth at an appropriate time, when all samples have been taken. All phlebotomy will be carried out by a qualified nurse at the HNU. A baseline venous sample of 80mL will be obtained for later determination of full blood count and glucose, as well as plasma (or serum) selenium levels, selected selenoenzyme activity, key selenium-responsive genes and protein levels and immune function markers**.** A saliva sample will also be collected from the volunteers after the blood has been taken, so the volunteer can stimulate their saliva glands by chewing sugar free gum while their blood is being taken. The volunteer will be asked to rinse their mouth out twice with cool water before chewing the gum and subsequently producing the saliva sample. The saliva samples will be used totest for a baseline of antibody titres to influenza antigens.

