After the consumption of a standard unit breakfast (a range of cereals, toasted bread, tea or coffee), the volunteer will be supplied with a 6 week supply of their Se-yeast tablets and a container for carrying out a 24hour urine collection prior to their next visit in week six. The volunteer will not know what dose of selenium they will have been given neither will the scientist (double blind).The volunteer will be advised to take one tablet everyday for the next 6 weeks, preferably with meals. The volunteer will be given a record sheet to indicate at which time of each day they are taking their supplement. The volunteer will be advised to contact either [name] ([name]) or [name] ([name]) if they have any queries or problems associated with the Se-yeast tablets.

[figure not shown]
Prior to the start of week six (Day 42±2days), the volunteer will be contacted by telephone or e-mail and reminded when to start their 24hour urine collection, which they will bring with them when invited to the Institute again in the morning between the hours of 7:30 and 9:00am for their second fasted blood sample. No saliva sample will be collected in week 6.

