The volunteers taking part in the study will be given up to 5 meals with the same colour coding each week out of a minimum choice of 5 meals. All test meals will be prepared in a dedicated food preparation kitchen by the HNU diet cooks or in their absence by a member of the study team in possession of the Foundation Certificate in Food Hygiene, level 1. These dishes may include a beef carbonarde (beef in beer), three cheese pasta, ratatouille, shepherds pie and spaghetti bolognaise (sauce). The meals will be made with the enriched and the un-enriched onions and neither the scientist leading the study, nor the volunteer will know which type of onion they are consuming. Each set of meals i.e. the selenium-enriched and the un-enriched will be labelled by colour, for example all un-enriched meals labelled blue and all enriched meals labelled red.

The meals will be delivered to the homes of the volunteer once the volunteer’s capacity to store the food has been assessed, which will usually occur at the initial interview stage. For example if a volunteer has a large freezer compartment, then up to one month worth of food may be delivered in one go. If however the volunteer only has a small freezer box, then it may be more appropriate to deliver food on a weekly basis. All deliveries of food will be made either by refrigerated van or by a member of the study team; alternatively volunteers will be offered the option to pick up the meals themselves from the Human Nutrition Unit at their own convenience. No extra meals will be provided for members of the family and spouses of the volunteers as the cost are prohibitive. The volunteers will be reminded that possible side effects to eating any onions are bloating and wind.

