**6.53 Compliance**

Meals will be provided and frequent contact with volunteers maintained during the intervention to check consumption of meals. The volunteers will be encouraged to inform us if they are not consuming the whole test meal. Volunteers will be given slightly more tablets than they will need in the blister packs. When the volunteers are invited back for their fasted blood in week six, they will be encouraged to bring the remainder of their blister pack so that we can issue a new set for the next six weeks and count the number of capsules they have consumed from the first set. A 24h urine sample will be collected midway through the intervention as selenium excretion is a good indicator of selenium intake. Serum/plasma selenium concentration will also be used as a check on compliance treatment.

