### 6.64 Saliva Samples: Humoral Response

**Detection of individual antibody forming cells by Enzyme linked immunospot (ELISPOT)**

Nitrocellulose filters will be coated with the appropriate dilution of viral protein or control antigen diluted in phosphate buffer saline. After incubation at 4oC overnight, plates are washed 3x with 300µL PBS-T per well. Background controls consisting in wells incubated under the same conditions but with PBS only are included in each plate. Plates are blocked with 200µL /well of complete medium for 30min-1h at 37oC and rinsed in PBS. This is followed by incubation with lymphocytes at different concentration for 4-6 hours at 37oC. Individual antibody forming cells (AFC) will be then detected by the addition of enzyme-labelled antibodies specific for different isotypes (IgA/G/M) Immunospots will be by the addiction of appropriated enzyme (alkaline phosphatase or HRP)-labelled antibody. Immunospot will then visualised by the addition of the appropriate enzyme colour development reagents. The substrate reaction will be stopped by rinsing and filters will be air-dried the spots enumerated either automatically or manually by inspection under dissecting microscope.

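### One visible letter per tablet arm (and one colour per onion arm), with unmasked post-baseline selenium as a compliance check, means the claimed double blind can fail for a whole arm at once

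*Protocol*

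**What the plan says.** **Tablets.** Section 6.52 states: "The supplements will be supplied blind to the Institute and labelled either A, B, C or D". The letter reaches the volunteer: "The volunteers will receive their supplements in a blister pack labelled either, A, B, C or D". Section 6.1 says the tablets are identical except for "alphabetical labelling which will be carried out at manufacture". Section 4.1 states: "The Se-yeast treatment will take place over 3 years". There are four tablet arms (50, 100 and 200 µg/day and placebo), so four letters mean one letter per arm. No pack number per volunteer and no change of letters between project years is described.

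**Onions.** Section 6.51 gives each onion type one colour, for example "all un-enriched meals labelled blue and all enriched meals labelled red". The onion arms run in years 2 and 3 only. Their code is to be kept by a scientist outside the project until the study ends.

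**Blinding claim.** Section 6.1 says the volunteer will not know "what dose of selenium they will have been given neither will the scientist (double blind"). Section 6.52 adds that double-blind assessment will avoid assessment bias.

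**Compliance.** Section 6.53 states: "Serum/plasma selenium concentration will also be used as a check on compliance treatment". It also uses a 24-hour urine collection midway through, on the ground that selenium excretion indicates intake. Section 6.61 has selenium measured in house. No section says who reads the post-baseline values or from whom they are withheld.

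**Code break.** Under Section 6.52 the unit manager holds a copy of the tablet code, for use if a serious adverse event makes the dose needed.

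**The concern.** A code shared by a whole arm is only as safe as its weakest disclosure. Whatever is learned about one volunteer's letter applies to everyone who carries it, in every year that the letter is used.

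There are two routes to disclosure. The first is the selenium data: the protocol expects plasma selenium to rise with dose, and it asks for that variable to be looked at for compliance. Anyone holding both the letters and the post-baseline values can average by letter. The second is an emergency code break, which needs no selenium data at all.

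At stake is the conduct of staff who know the letter: their contact with volunteers, how hard they pursue compliance queries, and any endpoint read by eye. Section 6.64 leaves room for such a reading, with "the spots enumerated either automatically or manually by inspection under dissecting microscope". Antibody-secreting cells are among the response variables named in the power section.

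**Working it through.** The protocol states no figure for the security of the code, so there is none to reproduce. The check asks how well letter means would identify the arms under the protocol's own assumptions.

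**Inputs**
- Volunteers per letter: Table 1 (Section 6.4) gives 32 tablet volunteers a year. Section 7.0 spreads the four arms evenly, so 32 / 4 = 8 per letter per year and 8 × 3 = 24 in all.
- Volunteers per onion colour: 12 a year, 24 in all (Table 1).
- Effect: Section 7.0 takes a range of 1 SD between extreme groups (11.7 for plasma selenium), proportional to dose. In SD units the expected means are 0 (placebo), 0.25 (50 µg), 0.5 (100 µg) and 1 (200 µg). Enriched onions count as 50 µg and un-enriched as none, so 0.25 against 0.
- Assumption: every volunteer contributes one post-baseline value. Drop-out would lower the probabilities.

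**Method.** Each letter mean is Normal(dose fraction × range, SD/√n). Rankings of four letters were simulated. Two-group orderings use Φ(d / √(2/n)).

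**Tablet letters, range 1 SD**

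| Event | Pure guess | n = 8 | n = 24 |
|---|---|---|---|
| 200 µg letter has the highest mean | 1/4 = 0.25 | 0.80 | 0.96 |
| Placebo letter has the lowest mean | 1/4 = 0.25 | 0.63 | 0.79 |
| Both extremes correct | 1/12 = 0.08 | 0.50 | 0.75 |
| All four in order | 1/24 = 0.04 | 0.32 | 0.59 |

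**Onion colours, range 1 SD** (pure guess 0.50)
- n = 12: Φ(0.25 / √(2/12)) = Φ(0.61) = 0.73
- n = 24: Φ(0.25 / √(2/24)) = Φ(0.87) = 0.81

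**Sensitivity to the range.** The protocol gives no expected plasma response beyond the 1 SD design value, so larger ranges are assumptions.

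| Range | Event | n = 8 | n = 24 |
|---|---|---|---|
| 2 SD | 200 µg letter highest | 0.98 | above 0.99 |
| 2 SD | All four in order | 0.67 | 0.92 |
| 3 SD | All four in order | 0.86 | 0.99 |

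**Code break.** One disclosure covers every holder of the letter: up to 24 of 4 × 24 = 96 tablet volunteers, or 25%. With a code per volunteer it would cover 1 of 96.

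**The case against.** The strongest reply is that no section gives letter-aware staff running access to post-baseline selenium. The weekly batches in Section 6.61 are tied mainly to screening. Section 6.1 describes the baseline sample as being for later determination. A compliance check could wait until the study ends. This stands: the blind is not shown to fail. But a compliance check implies that someone reads the values, and the protocol neither names that person nor restricts access. Section 5.4 restricts the link from code to identity, not the link from letter to selenium result.

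Nor is any tube or plate said to carry the letter, and manual counting is only one of two options. This also stands: biased assay reading requires a reader who knows the letter. The onion code is better protected, its colours are only examples, and they could change between the two years. The code-break figure is an upper limit. It counts volunteers who have finished or are not yet recruited, and it matters only to those who learn of the disclosure.

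A reader might infer three stronger things that the documents do not support.
- *Year 1 decodes the letters with about 98% certainty.* Φ(1/√(2/8)) = 0.977 is the chance that two letters already known to be placebo and 200 µg fall in the right order. Staff would face four unknown letters, for which the table above applies.
- *Allocation is no longer concealed.* Knowing what a letter means does not reveal which letter the next volunteer will draw. That needs a foreseeable sequence, and none is described.
- *Most of the trial is exposed after year 1.* Tablet volunteers in years 2 and 3 number 64 of 144 (44%). Year-1 tablet results cannot decode the onion colours.

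**Conclusion.** The point holds as a weakness in how the blind is protected, not as evidence that it is broken. One letter per tablet arm is stated. That it stays the same for three years is inferred from labelling at manufacture and the absence of any re-coding.

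At the protocol's design effect, one year of selenium results would single out the 200 µg letter about four times in five, but would order all four letters only about one time in three. The onion colours are less easily decoded. A plasma response larger than 1 SD would raise all these figures. The code-break route does not depend on them.

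The parts exposed are contact with volunteers, compliance queries and any manual spot counting by staff who know the letter. The change is worth making because unblinding of this kind cannot be repaired in the analysis and is cheap to prevent.

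**What to change.** 1. Replace the arm letters and colours by pack codes specific to each volunteer. If that is not feasible, use several codes per arm and renew them each project year.
2. Have the code list for tablets and onions held by a scientist outside the project, as Section 6.51 already foresees for the onions.
3. State that a code break is made for a single pack and discloses only that volunteer's allocation.
4. State that post-baseline plasma and urinary selenium results are withheld from staff in contact with volunteers and from immune-assay readers until the last week-12 sample has been read. Name who checks compliance from these values in the meantime.

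The cost is over-labelling of packs and meals, a longer code list and a few sentences in Sections 6.51 to 6.53. No extra volunteers or assays are needed. The change has to be settled before packs are labelled.

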**6.53 Compliance**

Meals will be provided and frequent contact with volunteers maintained during the intervention to check consumption of meals. The volunteers will be encouraged to inform us if they are not consuming the whole test meal. Volunteers will be given slightly more tablets than they will need in the blister packs. When the volunteers are invited back for their fasted blood in week six, they will be encouraged to bring the remainder of their blister pack so that we can issue a new set for the next six weeks and count the number of capsules they have consumed from the first set. A 24h urine sample will be collected midway through the intervention as selenium excretion is a good indicator of selenium intake. Serum/plasma selenium concentration will also be used as a check on compliance treatment.

## 6.6 Sample Analysis

### 6.61 Selenium Determination

Selenium determination will be carried out “in house” on an Agilent 7500C ICP/MS. This instrument is fitted with an octapole collision cell enabling elimination of interferences caused by argon dimmers around mass 80. Serum/plasma samples for total selenium status will be collected over a period of one week (one batch) and the analysis will be carried out at the end of that week. Depending on the number of volunteers screened in a particular week, the number of serum (or plasma) samples per batch could vary.

**6.61i Determination of Selenium in Serum/plasma (and urine).**

Selenium in serum/plasma (and urine) samples will be measured following the method of Delves and Sieniawska (1997), with refinement and improvement where possible. This will involve a simple 1 in 15 dilution of 200μL volumes of serum (or plasma) with a diluent containing 1.0% v/v butan-1-ol; 0.66% Triton X-100; 10mMol dm-3 NH3, 0.2mMol dm-3 (NH4)2H2 EDTA and 2 mMoldm-3 NH4H2PO4. This enables the ICP-MS to provide accurate and precise measurements of total selenium concentrations. Interferences from argon-adduct ions are further reduced by the presence of butan-1-ol in the diluent.

**6.61ii Determination of Selenium in onions and meals.**

Determination of total selenium in onions and the test-meals will follow a method described by Shah *et al* (2004), involving the digestion of the sample with nitric acid and hydrogen peroxide. The basic method may include refinements and improvements where possible. Quantification will be carried out by standard addition.

A separate project will be looking at selenium speciation Gammelgaard *et al* (2002) using ion pairing HPLC/ICP/MS.

### 6.62 Blood Samples

**6.62i Selenoprotein and Se-biomarkers analysis**

**Preparation of plasma, erythrocytes and platelets from whole blood**

Blood samples will be fractionated by centrifugation and samples of platelets, erythrocytes and plasma will be prepared as described previously (Fox, 2002).

**Platelet separation**

Whole blood samples will be collected and transferred to an EDTA containing Vacutainer TM tube (Becton Dickinson) and kept at room temperature for no longer than 30 minutes before centrifugation at 10g for 17 minutes to separate the erythrocytes from the plasma. The plasma layer containing the platelets will be transferred to a 1.5mL cryovial for a second centrifugation step at 900g for 12 minutes (room temperature) to separate the platelets. The plasma will then be removed by aspiration and the platelet pellet will be washed twice with modified Hanks buffer pH7.3 followed by centrifugation at 900g for 12 minutes at 4oC. The pellet will then be re-suspended in 200L 0.32M sucrose solution and stored under liquid nitrogen until analysis with the other blood fractions as one batch per volunteer.

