**Analysis of glutathione peroxidase (GPx) activity**

GPx activity in blood samples will be measured essentially as described by Paglia and Valentine, 1967. All samples (erythrocytes, plasma and platelets) from one individual will be analysed in a single batch using a human reference serum sample (Seronorm) as an internal reference standard. Plasma samples will be added directly to the assay mixture without prior dilution whereas reconstituted erythrocytes (25L) will be diluted and incubated for 5 mins with 500L Drabkin’s reagent prior to addition to the assay. Platelet samples will be sonicated in ice-cold 50mM phosphate buffer pH 7.2 containing 4mM EDTA followed by centrifugation at 10000rpm, 4oC, the supernatant will then be diluted and treated with Drabkin’s reagent prior to assay. The reaction mixture will contain 1mM phosphate buffer pH 7.0, 0.01mM EDTA, 1U glutathione reductase, 5M glutathione, 0.25M NADPH, 2.5M tert-butyl hydroperoxide and 100L sample. The reaction will be carried out at 37oC and absorbance readings will be recorded at 340nm.

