**Determination of key Se-responsive protein levels**

Key Se-responsive protein levels will be analysed using appropriate proteomic techniques and using Western blotting techniques. Proteins from blood will be separated from blood using sodium-dodecyl sulphate polyacrylamide gel electrophoresis (SDS-PAGE) on a 12% NuPAGE Novex Bis-Tris gel (Invitrogen) and transferred to PVDF membrane (Millipore) following the manufacturer’s instructions. The membrane will be saturated for 1 hour at room temperature with Starting Block (TBS) blocking buffer (Pierce). Primary antibodies specific to Selenoprotein W1, Selenoprotein P and other key Se-responsive proteins will be used separately to probe the membrane, followed by a secondary horseradish peroxidase antirabbit IgG (Sigma). Protein bands will be visualised using chemoluminescence with a Supersignal West Pico Chemiluminescent substrate kit (Pierce) on a Fluor-S MultiImager (BioRad).

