# 7.0 Statistical Analysis

Power calculations were done so that, out of the six study groups, a difference of 1 standard deviation in response variable between the minimum and maximum responding groups would be reliably detected. For example, for plasma selenium, previous studies (Shortt et al, 1997) suggest that the population standard deviation is 11.7, and so our sample sizes are designed to give an 80% chance of detecting a range of plasma selenium between the six groups of 11.7. For antibody secreting cells/500,000 lymphocytes and specific serum antibody (both at day 7 post-vaccination) the corresponding standard deviations are 76 and 19 respectively (Cox et al, 1999).

The power calculations also assumed that any effect of selenium supplementation would be proportional to the amount of supplementation, with enriched onions being equivalent to a supplementation of 50µg/day selenium and the un-enriched onions equivalent to no supplementation.

The power calculations were also based on the assumption that the data would be analysed using a one-way ANOVA model, the grouping having six levels (control, 50µg/day selenium, 100µg/day selenium, 200µg/day selenium, enriched onions, non-enriched onions). In order to be able to detect a range of 1 standard deviation between the groups with a power of 80%, a sample size of 144 (or 24 in each group) is sufficient. This allows for a drop-out rate of 25%, or in other words, finishing with 18 subjects in each group.

In the unlikely event of there being a year effect, and thus the two onion groups (but not the control and supplementation groups) being potentially compromised,24 subjects in each of the remaining 4 groups gives a power of 80% of detecting a range of 1 standard deviation in the response variable. This is based on using a two-way ANOVA model to analyse the data, with a three level year effect and a four level group effect (control, 50µg/d Se, 100µg/d Se, 200µg/d Se). It is important to stress however that we are aiming to recruit the full complement of 24 volunteers without the drop out rate of 25% as we feel there is a greater chance of compliance with the supplementation intervention.

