In order to allow for the unlikely possibility of a year effect the control group and each of the three selenium supplementation groups will be evenly and randomly spread over the three years. Unfortunately due to time constraints, this is not possible with the onion groups which will be evenly and randomly spread over only two of the years (i.e. half in each year). The two onion groups will also be able to be analysed separately, but with a reduced power of 18 subjects per group gives a power of 80% of detecting a difference in response variable of 1 standard deviation. This is quite a large effect of the enriched onions, given that they are only “equivalent” to a selenium dose of 50µg/day. This is based on a 25% drop out rate expected for the onion intervention study.

The data would be initially analysed using an ANOVA model to test for differences in end-points between the groups. If the required data assumptions for this model are not met (e.g. normality), then data transformations and/or non-parametric methods will be employed. A repeated measures analysis using all 5 data points per subject will also be used, although it is the end-point (week 12) that is of primary interest.

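### Keeping each volunteer's selenoenzyme samples in one batch protects within-volunteer change, but the week-12 group comparison does not use that, and nothing balances groups over assay runs

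*Protocol*

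**What the plan says.** In Protocol section 6.62i, under platelet separation, platelets are "stored under liquid nitrogen until analysis with the other blood fractions as one batch per volunteer". Under the GPx assay, all fractions "from one individual will be analysed in a single batch using a human reference serum sample (Seronorm) as an internal reference standard". Two other assays name a calibrator: GPx4 is quantified against PLPC-OH standards, and thioredoxin reductase (TrxR) is read from a curve made with the pure enzyme. The GPx1 section names no reference of its own.

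Section 7.0 sets the analysis: "The data would be initially analysed using an ANOVA model to test for differences in end-points between the groups". It names week 12 as the time point of main interest and adds a repeated measures analysis of all five time points. No baseline term is stated for the ANOVA. The protocol does not say whether an assay run may hold several volunteers, or how groups are spread over runs. Plasma selenium is handled differently, in weekly batches (section 6.61).

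**The concern.** If all of a volunteer's samples share a run, they share that run's error. The error drops out when one of the volunteer's time points is compared with another. It stays in full when that volunteer's week-12 value is compared with another volunteer's from a different run. The laboratory layout therefore serves change from baseline, while the analysis of main interest compares volunteers at a single time.

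The aim in section 1.0 includes finding functional markers of selenium status, and the selenoenzymes are candidates. Avoidable run variance lowers the chance of seeing a dose effect. Because it can differ by assay, one marker might look less responsive than another only because its runs were noisier.

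**Working it through.** **Inputs.** From section 7.0: six groups; effect proportional to dose, with enriched onions counted as 50 µg/day and un-enriched as none; target "a difference of 1 standard deviation in response variable between the minimum and maximum responding groups would be reliably detected"; 24 per group, or 18 after 25% dropout; 80% power. In SD units the means are 0, 0.25, 0.5, 1, 0.25, 0. Their average is 1/3 and their sum of squared deviations is 0.7083. Assumed, because not stated: two-sided alpha 0.05, and k = between-run SD / between-volunteer SD.

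**The plan's own figure.** 18/(1 − 0.25) = 24 reproduces. Noncentrality is n × 0.7083 with 5 and 6n − 6 df:
- n = 18: 12.75 on 5 and 102 df gives 77.2%, slightly under the stated 80%. That shortfall is a separate matter.
- n = 24: 17.0 on 5 and 138 df gives 89.7%.

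**Adding run error, one volunteer per run.** Week-12 error variance becomes 1 + k², so noncentrality becomes n × 0.7083/(1 + k²).

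| k | 1 + k² | Power, 24 per group | Power, 18 per group |
|---|---|---|---|
| 0 | 1 | 89.7% | 77.2% |
| 0.3 | 1.09 | 86.6% | 73.0% |
| 0.5 | 1.25 | 80.8% | 66.0% |
| 0.75 | 1.5625 | 70.0% | 54.8% |

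**Change and baseline adjustment.** Let ρ be the within-volunteer correlation without run error. Week-12 and baseline values each have variance 1 + k² and their covariance is ρ + k².
- Change: 2[(1 + k²) − (ρ + k²)] = 2(1 − ρ), free of k.
- Baseline as covariate: (1 + k²){1 − [(ρ + k²)/(1 + k²)]²}. With ρ = 0.5 (assumed) this is 0.75 at k = 0, and 0.771, 0.80 and 0.84 at k = 0.3, 0.5 and 0.75. The rises are 3%, 7% and 12%, against 9%, 25% and 56% without baseline.

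**Bias.** In simulation with random allocation, 24 per group, one or six volunteers per run and run variance up to 0.5 of volunteer variance, type I error was 4.6% to 4.9%.

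**What balanced sets would give.** Table 1 has 32 tablet volunteers each year (8 per tablet group), and 12 per onion group in years 2 and 3 only. One-per-group sets are then 8 of four, 16 of six and 8 onion pairs: 32 sets. The within-set sums of squares of the means are 0.5469, 0.7083 and 0.03125.
- Fixed set blocks, 24 per group: 8 × 0.5469 + 16 × 0.7083 + 8 × 0.03125 = 15.96 on 5 and 144 − 32 − 5 = 107 df gives 87.0%.
- Fixed set blocks, 18 per group (6, 12 and 6 sets): 3.28 + 8.50 + 0.19 = 11.97 on 5 and 108 − 24 − 5 = 79 df gives 73.3%.
- Set as a random effect (generalised least squares, k from 0 to 0.75): 88% to 90% at 24 per group, and 75% to 77% at 18.

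**The case against.** Much of the case on the other side stands.

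- Keeping a volunteer's samples together is sound practice in an intervention study, and the planned repeated measures analysis benefits from it: a shared run effect, additive on the scale analysed, cancels from group-by-time. A reader might infer that no analysis can remove the run error. That is true only of the unadjusted week-12 comparison.
- A reader might infer that every run holds one volunteer. The text says that a volunteer's samples are not split; it does not say that a run holds nobody else. The power losses above are for the one-volunteer reading. If runs already mix volunteers, balanced runs would fit the present text, but nothing asks for them.
- Controls are stated: the reference serum for GPx, the PLPC-OH standards for GPx4 and the pure-enzyme curve for TrxR. Only residual run error counts, and its size is unknown. The reference serum is a weaker control for the cell fractions. Plasma enters the GPx assay undiluted, while erythrocytes are treated with Drabkin's reagent and platelets are also sonicated and spun. The protocol takes no serum sample through those steps.
- A reader might infer bias between groups. Allocation is random and masked, and the simulation shows none. Bias would need, for example, assay drift by calendar year, since the onion groups are absent in year 1. The protocol does not say when the assays are run, so this cannot be claimed.
- A reader might extend the point to the Western blots. That section states neither batching nor gel layout, so the documents do not support it.
- None of the three examples used for power is affected: plasma selenium is batched weekly and the other two are immune measures. No selenoenzyme is named as primary or given an SD.

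**Conclusion.** The point holds as a mismatch between laboratory layout and analysis, limited to the selenoenzyme outcomes. The batching favours change from baseline, the week-12 ANOVA of main interest makes no use of it, and group balance over runs is not addressed. The consequence is lost precision. Its size cannot be taken from the documents. Over the assumed range of k, and with one volunteer per run, the loss is about 3 to 20 points of power at 24 per group (89.7% to between 86.6% and 70.0%) and about 4 to 22 points at 18 (77.2% to between 73.0% and 54.8%). It would be smaller wherever the stated references and standards remove run error, or if runs already mix groups.

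**What to change.** In section 6.62i, keep each volunteer's samples together, and state that runs hold volunteers from several groups in random order. Balance the groups as far as recruitment and run capacity allow, by tablet letter or meal colour so that dose stays masked. Carry one pooled erythrocyte lysate and one pooled platelet lysate through every run.

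In section 7.0, for the week-12 analysis of these markers, fit run as a random effect and include the baseline value, already measured in the same run, as a covariate.

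The cost is longer storage in liquid nitrogen while runs are assembled, and a few pooled aliquots. No visit or blood draw is added. Fixed set blocks would cost about 3 to 4 points of power if run error were nil (89.7% to 87.0%, and 77.2% to 73.3%), because Table 1 does not allow complete sets of six throughout. A random run effect avoids nearly all of that.
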